# Implementing primary healthcare-based measurement, advice and treatment for heavy drinking and comorbid depression at the municipal level in three Latin American countries: final protocol for a quasiexperimental study (SCALA study)

**DOI:** 10.1136/bmjopen-2020-038226

**Published:** 2020-07-28

**Keywords:** primary care, substance misuse, depression & mood disorders

Uses a theory-based approach to tailor clinical materials and training programmes, creating city-based Community Advisory Boards, and user-based user panels to ensure that tailoring matches user needs, municipal services and coproduction of health.Tests the added value of embedding and implementing primary healthcare activity within municipal-based adoption mechanisms and support systems, and community-based communication campaigns.Has a longer time frame (18 months) than is traditionally used in implementation studies, to assess longer term impacts.Gives considerable emphasis to process evaluation, developing logic models to document the fidelity of all implementation strategies, and to identify, the drivers and barriers and facilitators to successful implementation and scale-up.Due to municipal-based political and technical considerations, we are unable to randomise the involved municipal areas. We adopt a quasiexperimental design, optimising comparator municipal areas for confounding, and by using propensity score matching.

## Introduction

This paper outlines the protocol for a quasiexperimental study^1^ to test the implementation of primary healthcare (PHC)-based measurement, advice and treatment for heavy drinking and comorbid depression at the municipal level in three Latin American countries, Colombia, Mexico and Peru (Scale-up of Prevention and Management of Alcohol Use Disorders and Comorbid Depression in Latin America (SCALA) study).

Heavy drinking is a cause of considerable disability, morbidity and mortality.^2^ Heavy drinking is a causal factor for some communicable diseases (including TB and HIV/AIDS), for many non-communicable diseases (NCDs, including cancers, cardiovascular diseases and gastrointestinal diseases) and for many mental and behavioural disorders, including depression, dementias and suicide.^3 4^

In PHC settings, two-fifths of people with heavy drinking have depression, with risks of incident depression higher for heavier as opposed to lighter drinkers.^5^ In addition to its role in the aetiology of depression, heavy drinking is associated with worsening the depression course, including suicide risk, impaired social functioning and impaired healthcare utilisation.^6^

Heavy drinking is also a major contributor to global health inequalities, with alcohol-related harm aggravated by lower socioeconomic status^7^ and extending beyond the individual drinker to families, communities, health systems and the wider economy. Tackling the multiple individual and societal level harms caused by heavy drinking is essential for achieving global targets of reducing deaths from NCDs by 25% between 2010 and 2025,^8^ more so as risk of exposure to harmful use of alcohol increases with increasing socioeconomic status.^9^ In line with tackling harm due to lower socioeconomic status, United Nations Sustainable Development Goals include Target 3.5, to strengthen the prevention and treatment of harmful use of alcohol, with two proposed indicators: coverage of treatment interventions (pharmacological, psychosocial and rehabilitation and aftercare services) for harmful use of alcohol; and per capita alcohol consumption.^10 11^

Countries in Latin America have the highest alcohol-attributable disease burden after Eastern Europe and sub-Saharan Africa, with particularly high risks in alcohol-attributable traffic injury including violence.^12^ The burden of alcohol-attributable diseases in Latin America lead to marked economic costs, with numerous calls to implement effective and cost-effective policies.^13^

A robust and extensive body of literature demonstrates the range of evidence-based strategies that can be implemented to reduce heavy drinking in healthcare settings.^14^ Questionnaire-based measurement and brief advice programmes delivered in PHC are effective^15^ and cost-effective^16 17^ in reducing heavy drinking. In addition to brief advice, treatment for heavy drinking includes cognitive behavioural therapy and pharmacotherapy, both of which are found to be effective in reducing heavy drinking.^18^ Were the proportion of eligible patients receiving advice and treatment for heavy drinking to increase to 30% of eligible patients, the prevalence of harmful use of alcohol could decrease by between 10% and 15% across OECD (Organisation for Economic Co-operation) and member countries.^19^ However, to date, measurement and brief advice and treatment programmes have failed to achieve widespread take-up.^19^

Two systematic reviews^20 21^ and two multicountry studies^22–24^ have demonstrated that the proportion of PHC patients whose alcohol consumption is measured, and of heavy drinking patients given advice can be increased by providing training and support to PHC providers, although from very low baseline levels, and with effects not generally sustained over the longer term. Moreover, while there has been some previous research in countries of Latin America,^25–30^ most implementation work to date has been undertaken in high-income countries. The SCALA study will build on previous evidence^31^ to fast-track scale-up research and practice in Latin American PHC settings.

Out of a range of implementation frameworks that include a sequential approach for scale-up, and that provide practical guidance for how to work with organisations, health systems and communities to implement and scale-up best practices,^32–39^ we adopt the Institute for Healthcare Improvement’s Framework for going to Full Scale, which identifies adoption mechanisms and support systems for use across sequential steps, and describes the implementation methods that can be used at each step.^40^

SCALA seeks to address three specific barriers to sustained implementation of PHC-based measurement, advice and treatment for heavy drinking. The first barrier recognises that most PHC-based programmes focus on providers alone, whereas successful implementation of health interventions within complex health system demands addressing a range of underlying structural and support systems.^40^ Phase IV of the WHO study on the identification and management of alcohol-related problems in primary care concluded that embedding PHC-based measurement and brief advice programmes within the frame of supportive community and municipal environments might lead to improved outcomes,^41^ although this has never been formally evaluated. Similar conclusions were reached by the European Optimising Delivery of Healthcare Interventions (ODHIN) study^42^ and the US-based Substance Abuse and Mental Health Services Administration Screening, Brief Intervention and Referral to Treatment initiative.^43–45^

The second barrier is that standard cut-off points for the frequently used alcohol measurement instrument, Alcohol Use Disorders Identification Test, 3-item consumption version (AUDIT-C)^46^ (commonly a score of five for both men and women, or five for men and four for women) to trigger advice are too low,^47^ being equivalent to an average daily alcohol consumption of about 20 g of alcohol (around two standard drinks) or less.^48^ Practitioners may well find it problematic to give advice at such levels, which would also have huge time implications, with one in three or four patients being eligible for advice in many countries, under this criterion.^24 49^ We have argued to adopt similar models to blood pressure, where cut-off points for managing raised blood pressure are often determined by levels of blood pressure at which treatment has shown to be effective.^50 51^ Similarly, cut-off points for brief advice could be the baseline levels of alcohol consumption found in the randomised controlled trials that have investigated the effectiveness of PHC-delivered brief advice. In the first Cochrane review of the topic that focused on PHC, mean baseline levels were 313 g of alcohol per week,^52^ equivalent to an AUDIT-C cut-off of 8.^48^

The third and final barrier concerns the cost of implementing measurement and brief-advice for heavy drinking in PHC setting. Although, alcohol advice and treatment programmes can lead to substantial reductions in healthcare costs,^16^ freeing considerable numbers of working age people from alcohol-related diseases,^19^ their initial implementation can require a significant time-commitment on the part of providers, in terms of both initial training requirements and the time taken to deliver advice in routine practice. The largest part of the costs of implementing measurement and brief advice for heavy drinking in PHC settings are directly caused by the time spent by the healthcare providers delivering this intervention.^53^ Moreover, this large amount of time is experienced by healthcare providers as an important barrier to deliver routine measurement and brief advice to their patients.^54^ As evidence suggests that shorter sessions of brief advice are not less effective compared with longer sessions,^52 55 56^ it seems that reducing the time spent by healthcare professionals in preparing for these sessions could be a viable strategy to increase the overall adoption and implementation of alcohol measurement and brief advice at PHC level.

Given the strong comorbidity between heavy drinking and depression, our protocol includes screening for depression for those patients identified as heavy drinkers, with appropriate referral or PHC support for treatment.^57–59^

In the SCALA study, we implement three interventions (independent variables) for the PHCU:

Intensity of clinical package and training (standard, vs short, vs none).Training of providers (present, vs absent).Community integration and support (municipal action present, vs absent).

The main outcome (dependent variable) is the cumulative proportion of the adult (aged 18+ years) population registered with the PHCU that has their alcohol consumption measured within the 18-month implementation test period (defined as coverage). Three hypotheses are to be tested.

### Hypothesis 1

Municipal action leads to more sustainable coverage. After 18 months, the difference in coverage between municipal action present and municipal action absent for those PHCU that receive training is larger than after 12 months.

### Hypothesis 2

In the absence of municipal action, PHCU that have received training obtain higher coverage than PHCU that do not receive training.

### Hypothesis 3

In the presence of municipal action, the short clinical package and short training do not lead to less measurement coverage than the standard clinical package and standard training.

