### Outcomes

#### Primary outcome

The primary outcome will be the cumulative proportion of the number of adults (aged 18+ years) registered with the PHCU that have their alcohol consumption measured with a completed AUDIT-C instrument during the study period (coverage). The number of adults registered is provided by the administrative office of the PHCU and includes all adult patients covered by the PHCU, whether or not they consult during the 18-month implementation test period.

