### Statistical tests of key hypotheses

#### Primary study goal

Multilevel regression analyses will be undertaken at 12 months’ time of the implementation test period, using cumulative results at months 1 to 12, and at 18 months’ time using cumulative results months 1 to 18. Both analyses will include covariates of country and results during baseline month, analysed at the levels of the PHCU by study arm, taking into consideration the hierarchical nature of the data. For any PHCU that drops out during the study, outcome values for subsequent measurement points will be set at the last value obtained.

##### Hypothesis 1

Municipal action leads to more sustainable coverage among PHCU that receive training. We will compare results on primary outcome after 18 months with results after 12 months between Arm 3 versus Arm 2 via regression.

Dependent variables:

For each PHCU, cumulative results of months 1–18 of number of patients whose alcohol consumption is measured with AUDIT-C per 1000 registered patients; and cumulative results of months 1–12 per 1000 registered patients.

Random effects:

Country as random intercept (test for inclusion).

Independent variables:

Proportion of consulting patients who have their alcohol consumption measured with a completed AUDIT-C instrument during the baseline measurement month.Condition:Municipal action (yes vs no).Covariate:Proportion of consulting patients who have their alcohol consumption measured with a completed AUDIT-C instrument during the baseline measurement month.

It is postulated that coverage for Arm 3 will be significantly higher than for Arm 2.

##### Hypothesis 2

Training leads to higher coverage than no training. For both months 1–12 and months 1–18, compare cumulative coverage as per primary outcome between Arms 1 and 2 via multilevel regression analyses.

Dependent variable

Cumulative results months 1–12, and cumulative results months 1–18 of number of patients whose alcohol consumption is measured with AUDIT-C per 1000 registered patients withPHCU.

Random effects:

Country as random intercept (test for inclusion).

Independent variables:

Condition:Training (Arm 2 vs Arm 1).Covariate:Proportion of consulting patients who have their alcohol consumption measured with a completed AUDIT-C instrument during the baseline measurement month.

It is postulated that coverage for Arm 2 will be significantly higher than for Arm 1.

##### Hypotheses 3

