### Sample size calculations for main hypothesis

As the outcome of the primary study goal is predicted to be Arm 3>Arm 2>Arm 1, we compared both Arm 2>Arm 1, and Arm 3>Arm 2.

Our power calculations are based on the following assumptions: given an average size of a PHCU of approximately 15 000 adults, with an average of 1500 new consultations per month, we expect a cumulative coverage after 12 months of 0.0325 of the registered adult population to have had their alcohol consumption measured in the control condition (Arm 1) (data extrapolated from month 3 and month 9 assessments of control group from ODHIN study;^22 24^ [name], personal communication). For the short clinical package and short training (Arm 2), we expect this to increase to 0.075 (data extrapolated from month 3 and month 9 assessments of training group from ODHIN study;^22 24^ [name], personal communication). Although the WHO Phase IV study predicts an additional beneficial impact of municipal support,^41^ precise empirical data is not available—however, we consider an estimate for Arm 3, with municipal support, to be 0.15, a proportion that would need to be achieved to consider municipal support to be worthwhile. To detect the difference between Arm 2 and Arm 1, assuming a design effect of 15 PHCUs (clusters) across the three municipal areas in Arm 2, with 15 000 patients (items), and 12 PHCUs (clusters) in Arm 1, with 15 000 patients (items), with an ICC for PHCUs of 0.03 (data from ODHIN study;^22 24^ [name], personal communication) we would have 82% power at a significance level of 5%.^87^ For the difference between Arm 3 and Arm 2 (15 PHCUs/clusters in each arm), we would have 96.5% power.

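### Hypothesis 1 reads sustainability from a gap in cumulative coverage, which widens whenever any Arm 3 advantage remains after month 12, and the analysis section states a different success criterion

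*Protocol article*

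**What the plan says.** The Introduction states Hypothesis 1 as "Municipal action leads to more sustainable coverage" and makes it operational as a condition at the end of the test period: "the difference in coverage between municipal action present and municipal action absent for those PHCU that receive training is larger than after 12 months".

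The outcome is cumulative. Under Primary outcome: "The primary outcome will be the cumulative proportion of the number of adults (aged 18+ years) registered with the PHCU". The denominator is all registered adults, whether or not they consult.

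Under Statistical tests of key hypotheses, the Hypothesis 1 analysis reads: "We will compare results on primary outcome after 18 months with results after 12 months between Arm 3 versus Arm 2 via regression". Its two dependent variables are nested. The 18-month one is "For each PHCU, cumulative results of months 1–18 of number of patients whose alcohol consumption is measured with AUDIT-C per 1000 registered patients". The 12-month one, which lies wholly inside it, is "cumulative results of months 1–12 per 1000 registered patients". The entry closes with the expected result: "It is postulated that coverage for Arm 3 will be significantly higher than for Arm 2".

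The sample size section assumes coverage of 0.075 in Arm 2 and 0.15 in Arm 3, in a paragraph that introduces its inputs as cumulative coverage after 12 months. It concludes: "For the difference between Arm 3 and Arm 2 (15 PHCUs/clusters in each arm), we would have 96.5% power".

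**The concern.** A cumulative count cannot fall, so a gap between two cumulative counts records what has already been accrued as well as what is still happening. A claim about sustainability concerns only the second. If the criterion is met by any residual advantage, an effect that is fading could be reported as more sustainable coverage.

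The two sections also disagree on what decides the hypothesis. The Introduction asks for a gap that grows. The analysis section asks for Arm 3 to be higher than Arm 2. These can give different answers on the same data, and the second says nothing about months 13–18 specifically.

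This matters because the Introduction presents the study as addressing barriers to sustained implementation, and notes that earlier effects of training and support were generally not sustained. Hypothesis 1 is where that question is tested.

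**Working it through.** **Inputs from the sample size section.** Coverage at month 12: Arm 1 0.0325, Arm 2 0.075, Arm 3 0.15. ICC 0.03; 15 000 adults per PHCU; 12 PHCUs in Arm 1 and 15 each in Arms 2 and 3; significance level 5%.

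**Assumptions not in the plan.** Accrual is linear within each period, coverage does not saturate, and Arm 2 keeps its rate after month 12. Tests are two-sided.

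**1. The plan's power figures reproduce.**
- Design effect = 1 + 14 999 × 0.03 = 450.97.
- Effective n = 15 × 15 000 / 450.97 = 498.9 for 15 PHCUs, and 399.1 for 12.
- Arm 3 vs Arm 2: SE = √[(0.15 × 0.85 + 0.075 × 0.925) / 498.9] = 0.01986; z = 0.075 / 0.01986 = 3.78; power = Φ(3.78 − 1.96) = 96.5%.
- Arm 2 vs Arm 1: SE = √[0.0325 × 0.9675 / 399.1 + 0.075 × 0.925 / 498.9] = 0.01476; z = 0.0425 / 0.01476 = 2.88; power = 82.1%.

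So 96.5% is the power to detect 0.15 against 0.075 at one time point.

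**2. What the Introduction's criterion measures.**
Gap(18) − gap(12) = Arm 3 accrual in months 13–18 minus Arm 2 accrual in months 13–18.

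At the 12-month rates, six months add 0.075 in Arm 3 and 0.0375 in Arm 2, an excess of 0.0375. If a fraction *f* of that excess is kept, gap(18) = 0.075 + 0.0375*f*.

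| Excess kept | Gap at month 12 | Gap at month 18 |
|---|---|---|
| 100% | 0.075 | 0.1125 |
| 50% | 0.075 | 0.0938 |
| 25% | 0.075 | 0.0844 |
| 20% | 0.075 | 0.0825 |
| 0% | 0.075 | 0.075 |

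In the 20% row, Arm 3 accrues 0.0375 + 0.0075 = 0.045 in six months. At its earlier rate it would have accrued 0.075, so it has lost 40% of its own activity. Arm 2 has lost none. The gap has still grown.

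**3. Power of a significance test on that change.** The result depends on how PHCU variation carries into months 13–18, which the plan does not say. Two cases bracket it: ICC 0.03 applied afresh to the six-month increment, and PHCU rates that persist perfectly.
- All excess kept, ICC 0.03 on the increment: SE = √[(0.0375 × 0.9625 + 0.075 × 0.925) / 498.9] = 0.01454; z = 2.58; power 73%.
- All excess kept, persistent rates: SE = 0.5 × 0.01986 = 0.00993; z = 3.78; power 96.5%.
- Half kept: 29% and 61% respectively.
- A quarter kept, ICC 0.03: SE = √[(0.0375 × 0.9625 + 0.046875 × 0.953125) / 498.9] = 0.01272; z = 0.009375 / 0.01272 = 0.74; power 11%.
- A quarter kept, persistent rates: Arm 3's increment is 0.046875 / 0.15 = 0.3125 of its 12-month value and Arm 2's is 0.5. SE = √[(0.3125² × 0.1275 + 0.5² × 0.069375) / 498.9] = 0.00773; z = 1.21; power 23%.

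**4. The analysis section's criterion (Arm 3 above Arm 2) at month 18, with the effect gone after month 12.** Arm 2 reaches 0.075 + 0.0375 = 0.1125. Arm 3 reaches 0.15 + 0.0375 = 0.1875.
- Plan's formula: SE = √[(0.1125 × 0.8875 + 0.1875 × 0.8125) / 498.9] = 0.02248; z = 0.075 / 0.02248 = 3.34; power 92%.
- With persistent PHCU rates: the month-18 values are 1.25 and 1.5 times the month-12 values. SE = √[(1.25² × 0.1275 + 1.5² × 0.069375) / 498.9] = 0.02669; z = 2.81; power 80%.

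**The case against.** **The power statement is open about its contrast.** The sample size section says that it compares Arm 3 with Arm 2, and this matches the analysis section's own expectation. This stands. A reader might infer that 96.5% is wrong or misattributed. It reproduces, and the plan never calls it the power for the change in the gap. What remains is that the Introduction's version of Hypothesis 1 has no stated power.

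**A fading effect would often fail a significance test of the gap.** This also stands. A reader might infer that Hypothesis 1 would probably be confirmed despite heavy fading. Under the growing-gap test that is possible but unlikely (11–23% power with a quarter of the excess kept). Under the analysis section's level criterion it is likely. The flaw in the growing-gap test is what a positive result would mean.

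**Pre-existing differences between areas are addressed.** The analysis adjusts for the baseline-month measurement proportion, and propensity score matching is planned. A reader might infer that any constant difference between areas would pass as a sustained effect. The documents do not support that: the difference must favour Arm 3, and part of it may be adjusted away. Neither device separates a sustained effect from a fading one, however.

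**Model detail may lie elsewhere.** The short variable list names no period term or interaction. A condensed article may leave these to the full plan, and two outcomes per PHCU could be handled by a difference score. Their absence is not part of this point. The two stated criteria still conflict whatever the model.

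**Sustainability is not ranked as the main claim.** Correct: the three hypotheses are unranked, and the sample size section describes the primary study goal as an ordering of arms. The point rests only on what Hypothesis 1 itself claims.

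**Conclusion.** The point holds. Under the Introduction's rule, a significant result would show that Arm 3 still measured more patients than Arm 2 in months 13–18. It would not show that Arm 3 held its level better. On the plan's figures and linear accrual, the gap rises by half (0.075 to 0.1125) with no change in rates, and by a tenth (to 0.0825) when 80% of the advantage is gone.

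The analysis section's criterion is a different one and is weaker as evidence of sustainability. With no effect at all after month 12, it would be met at month 18 with about 92% power by the plan's formula, or about 80% if PHCU rates persist.

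The direction of the first result is arithmetic and needs no assumption beyond a cumulative outcome on a fixed denominator. The sizes rest on linear accrual, no saturation and a constant Arm 2 rate. The power of the gap test also rests on how the ICC applies to the increment, so it is given only as a range. The 96.5% is correct for the 12-month level contrast and should not be read as covering sustainability.

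**What to change.** - State one criterion for Hypothesis 1, in the same words in the Introduction and in the analysis section.
- Base it on non-overlapping periods: for example, measurements per 1000 registered adults per month in months 13–18 against an earlier window (months 1–12 or 7–12), compared between Arms 3 and 2 by an arm-by-period contrast within PHCU.
- Fix in advance the reference window, the scale (difference or ratio) and what counts as more sustainable. The scale matters. A rate ratio that stays constant gives no interaction on the ratio scale, so the plan must say whether holding the advantage is enough or whether it must grow.
- Report the cumulative Arm 3 vs Arm 2 comparison as a separate effectiveness claim.
- State that the 96.5% applies to the 12-month level contrast (0.15 vs 0.075) and that no power is given for the sustainability contrast, or compute one over a stated range of ICC assumptions.

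**Cost.** Wording and analysis only, since tally sheets are already collected and reported monthly. The period contrast is likely to have less power than the cumulative level contrast, and the report should say so.

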#### During 18-month implementation period for Arms 1–4

##### Provider-based measurement and assessment of alcohol consumption and comorbid depression and record of advice and treatment given (tally sheets)

The same mechanism, for tally sheets used during the baseline measurement period will continue for each calendar month of the 18-month implementation period. Tally sheets will be delivered monthly to each PHCU to distribute to participating providers. Completed tally sheets will be collected at the end of each month. Following training in Arms 2–4, and municipal support in Arms 3–4, each provider determines use and completion of the tally sheets, with no additional prompting. Monthly data will be collected and reported with accumulation of coverage over time. Formal reporting will be undertaken at baseline, and for coverage achieved by month 12 and by month 18 of the 18 month implementation and test period. Tally sheets will include an identifying code of the provider, PHCU, country and study arm, but no identifying code of the patient. Data will be extracted and sent to the project’s data warehouse at Technical University Dresden on a monthly basis.

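### Hypothesis 1 judges sustainability by growth of a cumulative coverage gap, which shows only that Arm 3 added more coverage than Arm 2 in months 13–18

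*Protocol article*

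**What the plan says.** The Introduction states Hypothesis 1 in two sentences. The claim is "Municipal action leads to more sustainable coverage". The criterion, judged at month 18, is that "the difference in coverage between municipal action present and municipal action absent for those PHCU that receive training is larger than after 12 months". The same section fixes the scale: "The main outcome (dependent variable) is the cumulative proportion of the adult (aged 18+ years) population registered with the PHCU", counting those measured within the implementation period.

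The Hypothesis 1 paragraph under Primary study goal keeps that scale: "We will compare results on primary outcome after 18 months with results after 12 months between Arm 3 versus Arm 2 via regression". Its first dependent variable is "cumulative results of months 1–18 of number of patients whose alcohol consumption is measured with AUDIT-C per 1000 registered patients"; the second is "cumulative results of months 1–12 per 1000 registered patients". It ends by postulating only that Arm 3 will have significantly higher coverage than Arm 2.

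The motivation is also in the Introduction. Earlier programmes raised measurement, but "with effects not generally sustained over the longer term". On data, the section on tally sheets during the implementation period says: "Monthly data will be collected and reported with accumulation of coverage over time".

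**The concern.** Sustainability is about what happens to activity over time: whether an arm keeps measuring patients, or whether the advantage of one arm over another lasts. A cumulative count cannot fall. The difference between two cumulative counts goes on growing for as long as one arm does more than the other in the new period, even if both are fading and the advantage is shrinking.

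This matters because Hypothesis 1 is the first hypothesis and addresses the problem that the Introduction names. It could be reported as confirmed when municipal action raised the level of activity but kept it up no better than training alone. A time term in the Hypothesis 1 model would not cure this, because a correct test of the growth in the gap would still be a test of who did more in months 13–18.

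**Working it through.** **Inputs.** All from the sample size section: 12-month coverage of 0.0325 (Arm 1), 0.075 (Arm 2) and 0.15 (Arm 3); 12, 15 and 15 units; 15,000 adults per unit; ICC 0.03; 5% level. Retention after month 12 and the period-to-period noise within a unit are not given, so they are assumptions shown as ranges.

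**The plan's own figures.** Design effect = 1 + 14,999 × 0.03 = 450.97. Effective numbers are 12 × 15,000 / 450.97 = 399.1 and 15 × 15,000 / 450.97 = 498.9. A two-proportion z test with unpooled variance, two-sided 5%, gives:
- Arm 2 v Arm 1: 0.0425 / 0.01476 = 2.88; power = Φ(2.88 − 1.96) = 82.1% (stated 82%).
- Arm 3 v Arm 2: 0.075 / 0.01986 = 3.78; power = Φ(3.78 − 1.96) = 96.5% (stated 96.5%).

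Both reproduce. They concern the level of coverage at 12 months, not the change in the gap.

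**What the criterion reduces to.** Write C for cumulative coverage.

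Gap(18) − Gap(12) = [C3(18) − C3(12)] − [C2(18) − C2(12)] = (Arm 3 coverage added in months 13–18) − (Arm 2 coverage added in months 13–18).

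The share of its earlier activity that each arm has kept does not enter separately.

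**Size under the planned values.** With flat rates in year 1, Arm 3 adds 150/12 = 12.5 and Arm 2 adds 75/12 = 6.25 per 1000 per month. If the arms keep fractions r3 and r2 after month 12, Gap(18) = 75 + 6 × (12.5 × r3 − 6.25 × r2) per 1000.

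| Case | Gap at 12 | Gap at 18 | Larger? |
|---|---|---|---|
| Both lose 50% | 75 | 93.75 | yes |
| Both lose 90% | 75 | 78.75 | yes |
| Arm 2 sustained, Arm 3 loses 25% | 75 | 93.75 | yes |
| Arm 2 sustained, Arm 3 loses 45% | 75 | 78.75 | yes |
| Arm 2 sustained, Arm 3 loses 50% | 75 | 75 | no |
| Arm 2 sustained, Arm 3 loses 60% | 75 | 67.5 | no |

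The gap grows when r3 > r2/2, so the break-even against a fully sustained Arm 2 is a 50% loss in Arm 3.

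**On the absolute scale.** Let activity fade by a fixed percentage per month from month 1, scaled to the same 12-month coverage.
- Both arms fade 10% per month: the monthly advantage falls from 3.28 per 1000 at month 12 to 1.74 at month 18, yet the cumulative gap rises from 75 to 88.8.
- Arm 2 fades 5% and Arm 3 fades 10% per month: the monthly advantage falls from 1.92 to 0.07, yet the cumulative gap rises from 75 to 79.3.
- Arm 2 constant and Arm 3 fades 8% per month: the gap falls to 71.8 and the criterion fails.

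**Chance of a significant result.** Simulation, 20,000 trials, 15 v 15 units; 12-month coverage beta-distributed with the planned means and ICC 0.03; months 13–18 increment = 0.5 × retention × coverage × lognormal noise with log SD 0, 0.3 or 0.6 (within-unit correlation about 1.0, 0.8 and 0.5); two-sided 5% t test on the increments.

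| Case | Corr. 1.0 | Corr. 0.8 | Corr. 0.5 |
|---|---|---|---|
| Equal retention, any level | 96% | 86% | 57% |
| Arm 2 sustained, Arm 3 loses 25% | 59% | 45% | 25% |
| Arm 2 sustained, Arm 3 loses 45% | 9% | 8% | 6% |
| Arms level at month 12, equal retention (Arm 3 favoured) | about 2% | about 2% | about 2% |

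A t test on log(increment / 12-month coverage) gave 2.2–2.8% in each tail under equal retention, close to the nominal 2.5%.

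**The case against.** The strongest reply is that the protocol defines its own term. The sentence after the claim says what more sustainable means, and nowhere is it defined as the share of its own activity that an arm keeps. What earlier studies failed to sustain were effects, and an effect is a contrast between arms. If Arm 3 fell back to Arm 2's rate, the gap would stop growing and Hypothesis 1 would fail, so the criterion does test something about persistence. That part stands. It does not rescue the label: on the absolute scale too, the criterion is met while the monthly advantage falls from 1.92 to 0.07 per 1000.

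Several stronger readings are tempting and are not supported:
- **That Arm 3 could fade at any speed and still pass.** It passes only while it adds more than Arm 2 in months 13–18. Close to that limit the expected gap still widens, but a significant result is unlikely (6–9%).
- **That equal fading always confirms the hypothesis.** This needs Arm 3 to be well ahead already. The 0.15 is not a forecast from data: the sample size section says that precise empirical data are not available and treats it as the level that would make municipal support worthwhile. If the arms are level at month 12, the chance is about 2%.
- **That a gap growing from 75 to 112.5 with no fading in either arm is a false confirmation.** It is a fully sustained doubling of activity and a poor example of the fault.
- **That fading would go unseen.** Monthly data are collected, the process evaluation names maintenance as a dimension, and the first secondary outcome relates measured to consulting adults over the same period. None of these is the Hypothesis 1 test, but differential fading could be found.

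Tests of retention also have less power than tests of level, which bears on the remedy.

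**Conclusion.** The point holds in a limited form. The Hypothesis 1 criterion shows whether municipal action still adds coverage in months 13–18. It does not show that coverage, or the advantage of municipal action, is better sustained, on either the ratio or the absolute scale. This follows from the nesting of the two cumulative outcomes and needs no assumption.

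The size does rest on assumptions: the planned 0.15 v 0.075, flat year-1 rates for the retention cases, 15 v 15 units, ICC 0.03 and a within-unit correlation that the document does not give. On these, equal fading is declared significant in 57–96% of trials and a 25% loss in Arm 3 alone in 25–59%.

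Hypotheses 2 and 3, the Arm 3 v Arm 2 comparison of level and the stated power are unaffected. The fault concerns what may be concluded from one test and can be cured by analysis or by wording, so it should be fixed but does not undermine the trial.

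**What to change.** Keep cumulative coverage for the comparisons of level. For Hypothesis 1, choose one of two changes.

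1. **Test sustainability directly.** For each unit, take measured adults per 1000 registered per month in months 13–18 and in one reference period fixed in advance (months 1–12). Compare Arm 3 with Arm 2 through an arm-by-period term in a log-link count model with a unit effect. The reference period must be settled beforehand, because months 1–12 and months 7–12 answer different questions. Report the result beside the level result, since a low rate that is well kept is not the aim either.
2. **Limit the claim.** Keep the 18 v 12 month cumulative gap, but reword the hypothesis and its conclusion to say that municipal action still adds coverage in months 13–18, and drop the words on sustainability.

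Neither needs new data, because monthly counts per unit are already collected. The cost of the first is power. Under the simulation model above, with a t test on the log ratio, one-third better retention in Arm 3 is detected with about 72% power at log SD 0.3 and about 24% at 0.6. Ratios are also noisy in units with very few measurements, which a count model handles better than a per-unit ratio. The second costs only wording, but leaves the question of sustainability untested.
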